**Primary outcomes (respondent: caregiver)**				
Child disruptive behaviors	Disruptive Behavior Disorder Rating Scale (screening only),(47) Iowa Conners Scale (169), Impairment Scale (170)		0.73–0.79; 0.61–0.69	B, 12, 24, 36

#### Qualitative component (Aim 3)

Semi-structured interviews will be conducted at 12-month follow-up to explore the experiences of children and their caregivers with the intervention and key multi-level factors (individual, family, contextual, and programmatic) that may have impacted their participation. A stratified purposeful sampling strategy (171) will be used to randomly select participants from the highest (*n* = 5) and lowest (*n* = 5) quartiles on the main outcome (DBD) across the three study arms (*n* = 10 per arm; a total of 30 children and their caregivers) to be invited for in-depth interviews. This sample size will be sufficient for theoretical saturation (172–174). This method will ensure that participants with varying experiences within the same study arm are represented; allow us to identify patterns and variations in participants’ experiences and further understand reasons behind those performing higher and lower on the main outcome (DBDs). In addition, semi-structured interviews will be conducted with purposively sampled contact teachers given their direct engagement with participants and study team during study implementation (see C.3.11). We will identify schools with the lowest (*n* = 3 schools) and highest (*n* = 3 schools) intervention attendance rates in each of the three study arms (6 × 3 = 18 schools). Contact teachers (*n* = 18) in each of these schools will be invited to participate in semi-structured interviews exploring: (1) the perceived benefit of the intervention to the school; and (2) barriers and facilitators to implementation and uptake at the school level (e.g., resources, school readiness, and contextual relevance). Finally, we will invite one MFG facilitator from each of the 20 schools implementing MFG (*n* = 20 facilitators) to explore their experiences with the MFG-based FS intervention, including: barriers and facilitators to implementation and uptake at the individual (e.g., time, motivation, and competing demands), organizational level (e.g., resources and contextual relevance), and macro-level (e.g., cultural norms and stigma). All interviews will be conducted in English or Luganda based on participants’ preference. Each interview will last ∼60 min and will be audio-taped.

### Data analysis

#### Data quality assurance, initial analyses, and missing data

We will use MIS IDA Q (175) to check for data entry errors and missing values (175). Frequencies and measures of central tendency and variability will characterize the sample. We will address incomplete data with direct maximum likelihood (ML) and multiple imputation (MI) (175). Program code and results will be documented and archived to enable future access and dissemination.

#### Primary analyses for Aim 1

We hypothesize that: (1) H1a: Relative to participants in the MFG-based FS only group, participants in the combined EE + MFG-based FS will have lower mean levels of oppositional defiant disorders and functional impairment following the intervention; and (2) H1b: Relative to participants in the EE only group, participants in the combined EE + MFG-based FS group will have lower mean levels of oppositional defiant disorders and functional impairment following the intervention. To test hypotheses H1a–H1b, we will fit three-level linear mixed models (LMMs) to (1) the Iowa Connors measure of oppositional defiant disorder and (2) the Impairment Rating Scale (IRS). Each of these two models will include fixed effects for study arm, time, and their interaction. We will use random intercepts for School ID to account for clustering of persons within schools and include random intercepts, random slopes, and their covariance for person ID to account for clustering of repeated measurements within persons. To test H1a–H1b for each outcome we will perform two time-averaged comparisons of repeatedly measured observations across study arms to examine intervention effects over the duration of the post-intervention study period. Because two comparisons among the study arms will be evaluated per outcome, alpha (α) will be set at 0.05/2 = 0.025 for each of these planned comparisons.

#### Secondary exploratory analysis for Aim 1

While we do not have a formal hypothesis regarding the superiority of EE-only to MFG-based FS-only, when we fit the LMMs described above we will also explore whether EE only is superior to MFG-based FS only or vice versa. This exploratory comparison will be tested at α = 0.05.

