**Methods:**

The study uses an experimental, longitudinal design across 30 cluster-randomized primary schools to compare single and combination intervention options; influences of economic empowerment and family strengthening on economic, perceptual, and functioning mediators; and context-specific moderators. The study will be conducted with 900 Ugandan children in mid-upper primary school (10–14 years). The three study conditions (*n* = 300 each) are: (1) economic empowerment only (EE only), (2) multiple family group-based family strengthening only (MFG-based FS only), and (3) combined EE + MFG-based FS. The interventions will be provided for 12 months; and assessments will occur at baseline, 12, 24, and 36 months.

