#### Statistical power analysis

We used NCSS PASS (177) to estimate minimum detectable effect sizes for the LMMs proposed to test hypotheses H1a–H2b to fulfill specific Aims 1 and 2. For power analyses for the proposed LMMs we assumed power = 0.80, α = 0.05/3 = 0.025, and 3 repeated assessments from *N* = 720 participants from 30 schools based on conservatively assuming 20% attrition from our original sample of 900. Under these assumptions we computed the range of the minimum detectable standardized mean difference *d* as 0.24–0.29 for the LMM-based repeated measures analyses proposed to address Aims 1 and 2. For the mediation analyses proposed for specific Aim 2, we used NCSS PASS (177) to compute the minimum detectable standardized indirect effect *d* from a mediation analysis assuming power = 0.80, α = 0.05/2 = 0.025, and *N* = 720 participants following 20% attrition, yielding *d* = 0.33–0.37. Our proposed analyses have sufficient power to detect small to small-medium effects across a wide variety of possible analysis scenarios; these are similar to or smaller than effect sizes in the literature (178) and our studies (19, 104).

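### The primary mixed model names no baseline adjustment, so the post-intervention contrast gives up precision that baseline scores already collected could supply at almost no cost

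*Protocol article*

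**What the plan says.** The protocol article's section on primary analyses for Aim 1 specifies three-level linear mixed models for the Iowa Conners oppositional defiant measure and the impairment scale. On fixed effects: "Each of these two models will include fixed effects for study arm, time, and their interaction". The random part has a school intercept, and the models "include random intercepts, random slopes, and their covariance for person ID to account for clustering of repeated measurements within persons".

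The hypotheses concern level, not change: children in the combined arm "will have lower mean levels of oppositional defiant disorders and functional impairment following the intervention". The test consists of "two time-averaged comparisons of repeatedly measured observations across study arms to examine intervention effects over the duration of the post-intervention study period", and "alpha (α) will be set at 0.05/2 = 0.025 for each of these planned comparisons".

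The abstract states that "assessments will occur at baseline, 12, 24, and 36 months", and Table 2 lists the primary outcomes at all four visits. The power section works with "3 repeated assessments from" 720 participants in 30 schools. The Aim 2 section on mechanisms of change reuses the same three fixed effects for H2a and H2b. No baseline covariate or equal-baseline constraint is named in any of these sections.

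**The concern.** The baseline value of an outcome is usually among the best predictors of its later values. A model that estimates each arm's follow-up mean freely, without conditioning on baseline, leaves that information out of the arm comparison.

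Two things are at stake. One is precision: the same 900 children could give a narrower interval. The other is protection against chance imbalance. Only 10 schools are randomised per arm, and stratification is on school size and location, not on symptom level. If arms differ by chance at baseline, part of that difference carries into the unadjusted estimate. The Aim 2 mechanism analyses inherit the same model.

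**Working it through.** **Inputs from the article.** 720 children analysed in 30 schools, so 240 children and 10 schools per arm and 24 children per school; follow-up at 12, 24 and 36 months; α = 0.025 per comparison; power 0.80. **Assumed**, because the article does not give them: the correlation ρ between two visits of the same child, the school ICC, and a two-sided test.

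**1. The plan's own figure.** For an unadjusted mean of three follow-ups, with outcome SD 1,

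d = (z₀.₉₈₇₅ + z₀.₈₀) × √(2 × [24·ICC + (ρ − ICC) + (1 − ρ)/3] / 240).

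At ρ = 0.4 and ICC = 0.01 the bracket is 0.24 + 0.39 + 0.20 = 0.83, so the variance is 0.00692 and d = 3.083 × 0.0832 = 0.256. The stated range of 0.24–0.29 is reached with ICC of about 0.006–0.020 at ρ = 0.4, or about 0.003–0.017 at ρ = 0.5. It is therefore compatible with an unadjusted analysis, but it cannot be reproduced uniquely. (The power section equates 0.05/3 with 0.025. Since 0.05/3 = 0.0167, I used the 0.025 set in the analysis section.)

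**2. Does a baseline outcome row adjust the contrast?** I compared generalised least squares variances of the averaged 12/24/36-month contrast at ρ = 0.5.

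| | ICC 0 | ICC 0.01 |
|---|---|---|
| Baseline left out | 0.00556 | 0.00747 |
| Baseline as fourth row, free arm-by-time | 0.00556 | 0.00747 |
| Baseline means constrained equal | 0.00347 | 0.00386 |

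The first two rows are identical. If time is instead linear with random slopes, adding the baseline row changes the variance by only about 2–4% (for example 0.00622 to 0.00608).

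**3. Gain, equal correlations, no clustering.** Var(mean of three) = (1 + 2ρ)/3 and Cov(mean, baseline) = ρ, so the share of variance removed is 3ρ²/(1 + 2ρ).

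| ρ | Variance removed | SE reduction |
|---|---|---|
| 0.3 | 0.27/1.6 = 17% | 9% |
| 0.4 | 0.48/1.8 = 27% | 14% |
| 0.5 | 0.75/2.0 = 38% | 21% |
| 0.6 | 1.08/2.2 = 49% | 29% |

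**4. Gain, correlation r per year decaying as r^lag.** The share removed is (r + r² + r³)²/(3 + 4r + 2r²).

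- r = 0.3: 0.174/4.38 = 4% of variance, 2% of SE.
- r = 0.5: 0.766/5.50 = 14% of variance, 7% of SE.
- r = 0.7: 2.350/6.78 = 35% of variance, 19% of SE.

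**5. Effect of clustering.** With ICC 0.01 and school effects that are stable over time, the SE reduction is 16%, 22% and 28% at ρ = 0.3, 0.4 and 0.5. At ρ = 0.4 the minimum detectable d moves from 0.256 to 0.200. If baseline predicts only within schools, the bracket at ρ = 0.4 becomes 0.24 + 0.59 − 0.39²/0.99 = 0.676 against 0.83, an SE reduction of about 10%.

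**6. Plausible chance imbalance.** With 300 children per arm and 30 per school, the standard error of a baseline difference between two arms is √(2 × [1 + 29·ICC]/300). That is 0.09 SD at ICC 0.01 and 0.13 SD at ICC 0.05, against a planned detectable effect of 0.24–0.29.

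**The case against.** The strongest reply is that an unadjusted randomised comparison is valid, that covariate lists are often left to an analysis plan, and that the gain may be small. Visits are up to 36 months apart and random slopes generally make correlations vary over time. Only children who screen positive enrol, which may lower the correlation. Table 2 gives modest reliabilities, 0.61–0.69 at the lower end, which makes the top of the range doubtful for the impairment scale if those values belong to it. Schools are also stratified and allocated by restricted randomisation.

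Much of this stands, and it is why the gain is given as a range. It does not remove the point. The article does more than stay silent on covariates: it sets out fixed effects, random effects, contrast and alpha, and repeats the fixed effects for Aim 2. Restriction on size and location does not secure balance on symptom scores.

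Some stronger readings are tempting but unsupported:

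- **A single figure for the loss.** A reader might put it at 15–20% of the standard error. Without clustering and with equal correlations, that requires ρ of about 0.41–0.49, which the article does not give.
- **The three assessments in the power section as proof that baseline is unused.** Three follow-ups with baseline as a covariate would also be three repeated assessments. The count suggests only that baseline is not an outcome row.
- **Baseline wholly ignored.** The article does not say whether baseline is a level of time. If it is an outcome row, likelihood estimation can use it for children with missing follow-up, where up to 20% attrition is expected.
- **Bias.** Chance imbalance under randomisation is already reflected in the standard error.
- **An optimistic detectable effect.** Nothing here shows that; the stated range can be reached with small ICCs.

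**Conclusion.** The point holds as a matter of efficiency. As written, the primary contrast takes no baseline adjustment, and a baseline outcome row would not supply it under a free arm-by-time interaction. The comparison remains valid and unbiased.

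The forgone reduction in standard error is about 9–29% under assumed equal correlations of 0.3–0.6 without clustering, and about 2–19% under correlations of 0.3–0.7 per year decaying with lag. Stable school effects would raise it; baseline prediction confined to within schools would lower it. Every correlation and ICC used is an assumption. The direction is secure and the size is not. I would class this as a free improvement, not as an error that threatens the trial.

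**What to change.** Add one sentence to the Aim 1 analysis, using either of two forms:

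- Model the 12-, 24- and 36-month Iowa Conners and impairment scores with the child's baseline score of the same outcome, and preferably its school mean, as covariates.
- Keep four time points and constrain baseline means to be equal across arms.

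In both cases, test the average of the three follow-up contrasts. A change-from-baseline contrast is not a good substitute: at ρ = 0.4 without school effects its variance is 0.00667, against 0.00500 unadjusted and 0.00367 with baseline means constrained.

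Apply the same to H2a–H2b for mechanisms that have a true pre-intervention measurement. Exclude savings in the matched accounts: these accounts are given to children assigned to an economic empowerment group, so there is no pre-intervention balance to adjust for.

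The cost is one or two degrees of freedom, of which the school mean takes one of the 30 − 3 = 27 between schools. No new data are needed.

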#### Primary analyses for Aim 2: Evaluating the effects of the intervention on mechanisms of change

We hypothesize that: (1) H2a: Relative to participants in the MFG-based FS only group, participants in the combined EE + MFG-based FS group will have higher levels of family financial stability, parenting and protective family processes, and perceptions related to help seeking following the intervention; and (2) H2b: Relative to participants in the EE only group, participants in the combined EE + MFG-based FS group will have higher levels of family financial stability, parenting and protective family processes, and perceptions related to help seeking following the intervention. To test hypotheses H2a–H2b for mechanisms of change (e.g., asset ownership scale and food security) we will fit LMMs using the same fixed effects (study arm, time, and study arm-by-time interaction) and random effects for the school (random intercepts) and person levels (random intercepts, random slopes, and their covariance) as in the proposed H1 analyses described above. To test H2a–H2b we will perform two time-averaged comparisons of repeatedly measured observations of financial stability, parenting and protective family processes, and perceptions related to help seeking at α = 0.025 per comparison.

#### Primary analyses for Aim 2: Assessment of mediation of intervention effects

We will investigate whether family financial stability, parenting and protective family processes, and perceptions related to help-seeking constructs at 12 and 24 months mediate the relationship between intervention group assignment and DBD symptoms and behavioral functioning at 24 and 36 months, respectively. To maximize rigor, these analyses will be conducted using principles of structural equation modeling (SEM) and causal inference methods (176).

#### Secondary exploratory analyses: Moderation of intervention effects, including sex as a biological variable

All previously described inferential analyses will be repeated with models extended to include sex assigned at birth as a moderator to examine whether effects vary by participants’ sex. Additional moderators, including orphanhood status, connection to community, and utilization of religious and cultural resources, will be examined similarly. Alpha will be set to 0.05 for these exploratory analyses.

#### Secondary exploratory analyses for Aim 2: Comparing multiple family group-based family strengthening only to economic empowerment only

In the LMMs described above, we will also explore whether EE only is superior to FS only or vice versa at α = 0.05. We will also explore whether any observed EE only vs. MFG-based FS only difference is mediated and/or moderated by the potential mechanisms of change and moderators described above *via* SEM and causal mediation methods at α = 0.05.

#### Statistical power analysis

We used NCSS PASS (177) to estimate minimum detectable effect sizes for the LMMs proposed to test hypotheses H1a–H2b to fulfill specific Aims 1 and 2. For power analyses for the proposed LMMs we assumed power = 0.80, α = 0.05/3 = 0.025, and 3 repeated assessments from *N* = 720 participants from 30 schools based on conservatively assuming 20% attrition from our original sample of 900. Under these assumptions we computed the range of the minimum detectable standardized mean difference *d* as 0.24–0.29 for the LMM-based repeated measures analyses proposed to address Aims 1 and 2. For the mediation analyses proposed for specific Aim 2, we used NCSS PASS (177) to compute the minimum detectable standardized indirect effect *d* from a mediation analysis assuming power = 0.80, α = 0.05/2 = 0.025, and *N* = 720 participants following 20% attrition, yielding *d* = 0.33–0.37. Our proposed analyses have sufficient power to detect small to small-medium effects across a wide variety of possible analysis scenarios; these are similar to or smaller than effect sizes in the literature (178) and our studies (19, 104).

### Qualitative data analysis

Interviews will be transcribed verbatim and uploaded to QSR NVivo12 (179). Analytic induction techniques will be used for coding (156). Initially, 12 interview transcripts randomly selected across the study groups will be read multiple times and independently coded by the team using sensitizing concepts to identify emergent themes (open coding) (174). Broader themes will be broken down into smaller, more specific units until no further subcategory is necessary. Potential themes/subthemes include barriers and facilitators to the intervention participation at the individual-level (e.g., motivation, readiness to change, and time constraints); family level (e.g., competing demands and support); and program-level (e.g., content relevance; interaction with other program participants, site-specific concerns). For facilitator interviews, potential themes/subthemes include individual-level (competency, motivation, training, supervisory support, and readiness for change); and school-level (readiness, buy-in, and resources); and macro-level (e.g., cultural norms and stigma) facilitators and barriers. Similar themes related to school-level factors are expected in contact teacher interviews. Analytic memos will be written to further develop categories, themes/subthemes, and to integrate the ideas emerging from the data (174, 180). Codes and the inclusion/exclusion criteria for assigning codes (173) will be discussed as a team to create the final codebook. Each transcript will then be independently coded by two investigators to establish inter-coder reliability. A level of agreement ranging from 66 to 97% based on level of coding indicates good reliability (181). Disagreements will be resolved through team discussions. The secondary analysis will compare themes and categories within and across groups to identify similarities, differences, and relationships among findings. Member checking, peer debriefing, and audit trail will be used to ensure rigor (182).

### Data integration

Findings from qualitative and quantitative data analyses will be integrated at the interpretation and discussion stages (183). Conclusions and inferences will be synthesized for a more contextualized and thorough understanding of the participants’ experiences with the intervention. Data integration will serve two purposes: (1) *Complementarity* (184, 185); and (2) *Expansion* (184, 185). Qualitative findings will offer further explanations and context for findings from the quantitative analyses. The qualitative findings will: (1) expand on our understanding of attendance and participant satisfaction; and (2) inform our overall understanding of the impact of the intervention.

## Monitoring and responding to adverse events

The MPIs will train all study personnel in Uganda on identifying and identifying conditions that may jeopardize the welfare of study participants. Reporting of adverse events will occur according to a project protocol. For this study, safety and monitoring will be overseen by the project coordinator (based in Uganda), in-country co-investigator, and the MPIs. This group is expected to meet in person at least 2–3 times per year and will have weekly conference calls (using telephone, Zoom, and/or Skype). In the case of an adverse event, staff will inform the project coordinator immediately and the MPIs/in-country co-investigator within 24 h of the presence of a possible unanticipated adverse event. Any presence of a possible unanticipated adverse event will be immediately reported to the local research ethics committee in Uganda and Washington University Institutional Review. The IRBs will determine whether to stop the study protocol temporarily or provide suggestions and/or modifications to the study procedures. The research team will examine preliminary outcomes data on a quarterly basis to make sure there is no harmful impact on the study participants.

## Data management and integrity to protect confidentiality

To protect the integrity of the participants’ data, the following procedures will be followed. First, the data collected from the study participants will be used only for the purpose of research. All data will be kept confidential and will not be shared with anyone outside of the research team. Second, all participants will be assigned a code number, which will be used on all study-related documents and data collected from participants. Given the longitudinal nature of the study, we maintain lists of participants with links between identifying information and code numbers. Only the senior research team, comprising of the MPIs, in country co-investigator; project director (US)/coordinator (Uganda), and data manager will have access to these lists, which are kept in locked files. Other study personnel will have access on an as-needed basis to adequately perform their duties.

All study personnel will complete CITI Human Subjects Training, as well as training on data safety, participant confidentiality, limits of confidentiality, and proper administration of the study protocol. Hard copies of participants’ data will be stored in locked cabinets to which only the senior research team will have access. Only this group will have access to data entered into password protected computer files. All data use requests, will be reviewed by the MPIs. Only anonymized data, without identifying information will be shared. Study participants are notified of the above procedures in the informed consent/assent forms.

Participants are also informed of the limits of confidentiality, including mandatory reporting for child abuse and neglect under the Uganda law. Interviewers will receive training on the Ugandan laws regarding child abuse and/or neglect. Interviewers who suspect child abuse and/or neglect will be required to follow a specific reporting protocol intended to protect the safety of children, and at the same time reduce the risk that erroneous reports are made.

